## Abstract

The only treatment for celiac disease (CD) is a strict and lifelong gluten-free diet (GFD), which must be safe and nutritionally balanced. Avoiding gluten brings difficulties with following the diet and can affect the social life of people with CD. The Zeliakide Project is a nutrition education program aimed at increasing the knowledge of the general population about healthy diets, CD and GFD, and, therefore, to improve the social inclusion and quality of life of people with CD. It is a one-month intervention program, two-armed cluster, non-randomised and controlled trial, conducted among 10–12-year-old children. Pre- and post-intervention evaluation and 1 month follow-up will be carried out to assess the effectiveness of the program. It is based on competencies and their respective learning outcomes. The teaching methodology chosen is a STEAM methodology: inquiry-based learning (IBL). A teaching unit has been created to develop the project, which, in the future, will be useful for the self-application of the program. This study will provide a valid and useful tool to achieve changes in the diet at the school level and will help to promote the social inclusion of people with CD. Moreover, it will enforce the STEAM competences of children.

## 1. Introduction

Celiac disease (CD) is a systemic immune-mediated disorder caused by the ingestion of gluten and related prolamins in genetically predisposed individuals [1]. Its prevalence has increased significantly in the last 20 years [2,3] and it is not a well-understood disorder. In fact, this disease is sometimes undetected, with a 1:3-to-1:5 ratio between diagnosed and undiagnosed [4]. However, in most parts of the Western world, it affects approximately 1–2% of the population [5], even if wide differences have been found among countries and even regions [2,5,6].

Currently, the only treatment for the disease is a strict and lifelong gluten-free diet (GFD). Although the importance of the absence of gluten in the diet is obvious, the diet must remain nutritionally balanced in order to achieve an optimal health condition. Achieving a balanced diet is difficult for the general population. In the case of children and adolescents, for example, breakfasts and mid-morning snacks (very common in Spain) differ from the prototype of a healthy diet due to the excessive consumption of sweet foods [7,8,9]. Achieving a healthy diet is even more difficult for celiac patients. 

The GFD involves excluding certain foods from the diet, which can lead to nutritional deficiencies. In the Basque Autonomous Community (Northern Spain), we studied a cohort of patients with CD in a previous study and found that their diet was deficient in dietary fibre and complex carbohydrates and high in protein and saturated fats [7,8]. Similar results were found by other authors [9,10,11]. It should be noted that these dietary errors are also common in the general population. Even if guidelines for the general population are published frequently, specific guidelines for the celiac population (following restrictive diet) are much rarer [7,8]. 

In addition to guidelines, educational activities are necessary for the management of chronic diseases and represent one of the most recommended measures to address diseases, including CD [12]. These types of educational interventions rely on the competence of health professionals, and desirably, health professionals specialised in the area of education. 

The aim of these activities is to empower people suffering from the pathology and/or people close to the patient in the treatment of the disease, in order to maintain or improve their quality of life [12]. On the other hand, the main objective of education is to provide information, share practical knowledge and change behaviour, when needed. 

This educational process is fundamental in the CD, because apart from physical health, GFD greatly influences the quality of life of patients, especially at the social and family level [13]. One of the biggest handicaps is eating out, as it is difficult to find gluten-free dishes and to ensure that there has been no gluten cross-contact [14]. In addition, they feel socially excluded when they have to check their food offer or even refuse it when they are eating out because of their situation. Moreover, a study by Zarkadas et al. found that 80% of the members of a celiac association in Canada avoided eating out at restaurants [15]. Another study of the same group found that restaurant menus are limited and eating away from home remains problematic, even if the situation is slowly improving [16]. 

In any case, strict GFD is fundamental for the physical health of people with CD, but also for their mental health. In fact, Halmos et al. linked a lower risk of psychological distress to a higher adherence to the GFD, which is very important for a good quality of life [17]. In this line, some studies have reported that health education needs to be developed and provided to people with CD in order to enable them to cope with their situation [18,19]. However, mental health is also closely related to relationships, especially during childhood. Barrio et al. observed that one of the biggest concerns of Spanish children with celiac disease was the relationship with their friends [20]. In addition to impacting individuals who have celiac disease (CD), the condition also has an impact on the quality of life of those in their immediate circle. This is due to the influence of the disease on everyday activities, social interactions, financial aspects (as gluten-free products tend to be more expensive), and the anxiety experienced by caregivers [21,22,23].

For all of these reasons, a nutrition education program related to CD and GFD should aim at both physical and social health. Moreover, taking into account the high impact of the disease on the people close to the person with CD, as well as the importance of the behaviour of the society for their inclusion, education should be directed not only to the patient but also to the general population [16]. Even if several interventions aimed at the general population have been developed for the prevention and treatment of other diseases with a high prevalence, such as obesity [24,25,26,27], they are much scarcer in the case of CD.

Moreover, food habit interventions have a peculiarity: many of them target children, because it is during childhood that food habits and lifestyles are learned and established, and many of them focus on the school environment [25,26,27,28,29,30,31]. Currently, new educational approaches, such as STEAM, are being introduced in schools. The STEAM curriculum is based on the need to focus on Science (S), Technology (T), Engineering (E), Arts (A) and Mathematics (M) in a transversal and interdisciplinary way in order to transform teaching and learning processes into integrated and creative processes [32]. Moreover, this methodology is now being incorporated into nutrition education programs [33,34].

In view of the above, we present a nutrition education program aimed at increasing the knowledge of the general population in terms of healthy diet, gluten and CD, aiming to help improve the social inclusion and quality of life of people with CD.

## 2. Materials and Methods

### 2.1. Description

The Zeliakide project (the name comes from the union of two Basque words: “zeliako”, which means “celiac”, and “kide”, which means “companion”) is a one-month (4 weeks) intervention program, two-armed cluster, non-randomised and controlled trial, conducted among 10–12-year-old children with a pre- and post-intervention evaluation and 1 month follow-up to assess the effectiveness of the program.

The trial consists of a nutrition education intervention, focused on CD and the GFD. It is an intervention based on competencies and their respective learning outcomes. The teaching methodology chosen is inquiry-based learning (IBL). IBL enables children to acquire skills and knowledge through inquiry. It is a STEAM methodology that seeks to get children to ask questions, inspect, make measurements, design experiments, make logical reasoning based on evidence, and communicate the results.

The intervention is carried out by research experts in nutrition and CD, from the GLUTEN3S research team, and with experience in nutritional education activities. In addition, in order to highlight the role of women in science, they will be mainly women from this group who will go to the classroom to develop the intervention.

### 2.2. Participants

Healthy children in the fifth and sixth years (last cycle) of primary school (10–12 years old) will participate in the study. At this age, they actively work on the concepts of diet and nutrients in the school curriculum. In addition, they also start to work on scientific competence, so it is considered the most suitable time to carry out the intervention. 

Inclusion criteria to participate in the study will be that children study in a primary school that must be used to project based learning and show interest in participating in the project. In addition, schools must have at least one class in the 5th and 6th grades of primary school. The exclusion criterion is school students who have a family or close relationship with any of the GLUTEN3S team researchers.

### 2.3. Sample Size Calculation

Regarding knowledge acquisition, based on the results of a pilot experience of this program as well as other studies found in the bibliography, it has been estimated that to provide a power of 80% and an α error of 5% to detect a small–medium effect size (Cohen’s d of 0.32), 60 participants are required. Since detecting changes in attitude is more complicated, *n* = 120 participants will be proposed for such an outcome. Based in the dropout of similar studies [35,36,37], the final sample size will be increased by 20% to reach 144 children.

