### 2.8. Statistical Analysis

The description of the characteristics of the participants and data from the pre-, post- and retention test (one month after) questionnaires will be reported per group (control and intervention). 

For the analysis of the differences between groups, a variety of statistical tests will be used depending on the type of response to the questions (continuous, discrete or qualitative). Based on the distribution of the variables of interest in the sample, descriptive statistics for continuous data will be presented using the mean and standard deviation or the median and interquartile range. Qualitative data shall be presented as frequencies and percentages. Quantitative variables will be analysed using an ANOVA of repeated measures test using the group as a factor of the independent level (parametric) or Wilcoxon’s test segmenting by group (non-parametric). On the other hand, qualitative variables in two categories will be analysed with Chi-square and Cochran’s Q tests. Finally, qualitative variables in more than two categories will be analysed with Chi-square and McNemar Bowker’s tests.

Data will be entered and analysed using SPSS 28.0 software. A confidence interval of 95% and significance level of *p* < 0.05 will be assumed.

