The design of the study also took into account the results obtained in a previous pilot work conducted by the Gluten3S research team [40,65]. This procedure is fundamental to accurately estimate the required sample size and avoid involving an excessive or insufficient number of participants, ensuring that the intervention’s effect can be properly observed. Thus, it has been estimated that a total of 144 children should be included in the study in order to detect a small-to-medium increase in knowledge, such as an increase in approximately one point on a scale of 0–4; thus, a sample size of this magnitude is necessary. 

The teaching unit is a complete set of materials, such as a student’s and a teacher’s notebook with all the activities explained in detail and various games, especially designed for the Zeliakide Programme. It also includes an innovative augmented reality application to reinforce the use of IBL methodology. It is considered that this material may be useful for future interventions or didactic activities, and it will be freely available and accessible to anyone who wants to use it, upon request. Moreover, it can be easily used autonomously by teachers and trainers. 

Zeliakide does not forget the importance of family participation in nutritional education activities, since results of a meta-analysis revealed that interventions that included family members produced larger effects than interventions focusing only on children [61,72,73,74]. Therefore, the intervention presented here includes activities to be carried out at home to involve children’s parents and guardians. Besides that, two short sessions (60 min) per week will be held at school over a period of one month. It must be highlighted that it seems to be appropriate to transmit the information in small doses and spread out over time for optimal learning [29,72,75,76,77].

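### Section 2.3 gives 60 children 80% power at d = 0.32 without defining the effect; that power does not hold for the between-group difference a two-armed trial estimates

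*Protocol article*

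**What the plan says.** Section 2.3 sets the target for knowledge as "to provide a power of 80% and an α error of 5% to detect a small–medium effect size", and gives "Cohen’s d of 0.32), 60 participants are required". For attitude, which it calls harder to change, it says that "120 participants will be proposed for such an outcome", with no effect size or power attached. Citing dropout in similar studies, it then says "the final sample size will be increased by 20% to reach 144 children".

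The Discussion confirms that 144 is the study total: "it has been estimated that a total of 144 children should be included in the study". It ties that number to a small-to-medium rise in knowledge, of roughly one point on a 0 to 4 scale. Section 2.3 had linked knowledge to 60, and attitude to 120 and then 144.

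Section 2.1 describes a "two-armed cluster, non-randomised and controlled trial, conducted among 10–12-year-old children", and section 2.5.2 plans a control group of similar size. Section 2.8 opens its test plan with "For the analysis of the differences between groups", uses repeated-measures ANOVA with group as the between-subject factor for quantitative variables (Wilcoxon within each group as the non-parametric alternative), and closes with "A confidence interval of 95% and significance level of" p < 0.05.

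**The concern.** A power statement has meaning only for a defined effect and test. This one names a Cohen's d and a number of participants and nothing else. In a two-armed trial that sets out to analyse group differences, most readers will take d = 0.32 as the difference between arms. On that reading 60 is far too few, and so are 120 and 144 unless baseline explains much of the outcome variance.

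The figure matters because the Discussion presents the calculation as what ensures that the effect can be properly observed. If the power is much lower for the controlled comparison, the trial's size is justified by a number that does not apply to its main contrast. A non-significant group difference would then say less than the stated power suggests.

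**Working it through.** **Inputs.** d = 0.32, power 80%, alpha 5%, and 60, 120 and 144 children (section 2.3); two arms of about equal size (sections 2.1 and 2.5.2); 95% confidence intervals with p < 0.05, taken as two-sided testing (section 2.8). The pre-post correlation, intraclass correlation and class size are not given, so values below are assumptions. Results use the noncentral t or F distribution unless a normal formula is shown.

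**Step 1: reproduce 60.**
- One group, pre-post, one-sided: ((1.645 + 0.842)/0.32)² = 60.4; the paired t-test needs 62, and 60 gives 79% power.
- One group, pre-post, two-sided: ((1.960 + 0.842)/0.32)² = 76.6; the paired t-test needs 79, and 60 gives 68%.
- Group-by-time interaction, f = d/2 = 0.16, three waves, noncentrality f² × N × 3/(1 − ρ): N = 65 at ρ = 0.5 (66 with equal arms), 58 at ρ = 0.55, 52 at ρ = 0.6. At N = 60 power is 77% at ρ = 0.5 and 81% at ρ = 0.55.

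So 60 is close to a one-sided, one-group test, or to the planned type of ANOVA with a correlation of about 0.55.

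**Step 2: what f = 0.16 means.** With two waves, the cell interaction effects are ±e and f = e/σ, so e = 0.16σ. The difference in change between arms is 4e = 0.64σ. At ρ = 0.5 the SD of change equals σ, so the value is 0.64 on either scale. This is twice 0.32.

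**Step 3: d = 0.32 as a difference between arms.** Normal formula: 2 × ((1.960 + 0.842)/0.32)² = 153.3, so 154 per arm; the t-test gives 155 per arm, 310 in total. For the planned sizes, two-sided 5%, no clustering:

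| Analysed (total) | Per arm | Power at d = 0.32 | d detectable at 80% |
|---|---|---|---|
| 120 | 60 | 41% | 0.52 |
| 144 | 72 | 48% | 0.47 |

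Reading 60 as a per-arm number gives the first row. Reading it as a total (30 per arm) gives 23%.

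**Step 4: adjust for baseline.** Multiply the variance by 1 − r².
- r = 0.5 (assumed): 116 per arm needed; power with 120 is 52%; detectable d = 0.516 × √0.75 = 0.45.
- r = 0.7 (assumed): 80 per arm needed; power with 120 is 68%.
- A total of 120 reaches 80% only near r = 0.8 (83%). A total of 60 needs r of about 0.9.

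**Step 5: clustering.** Section 2.3 mentions no design effect. With 20 children per class (assumed), 1 + 19 × ICC is 1.19 at ICC 0.01 and 1.95 at ICC 0.05. Any positive ICC lowers the powers in steps 3 and 4.

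**Step 6: the one-point target.** One point at d = 0.32 implies an SD of 1/0.32 = 3.1. A score bounded by 0 and 4 has an SD of at most about 2 (half the children at each end), so one point between arms is d of at least 1/2 = 0.5. The two statements of the target do not match on a single score.

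**Step 7: enrolment.** 120 × 1.20 = 144, as stated. It keeps 120 if losses do not exceed 1 − 120/144 = 16.7%.

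**The case against.** The article never says that d = 0.32 is a difference between arms. It speaks of acquiring knowledge and of changes in attitude, and the planned analysis is repeated-measures ANOVA, not a two-sample t-test. With that test, three waves and an ordinary correlation of about 0.55, 60 follows. This stands. A reader might infer that 60 is an arithmetic error under any reading, and the document does not support that. The fault is an effect that is undefined or mislabelled: on this route f = 0.16 is not a 0.32 SD difference between groups.

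The one-point target also weakens any claim that the trial is severely underpowered. If a one-point difference between arms is what matters, d is at least 0.5, and unadjusted power before clustering is at least 78% with 60 per arm and 85% with 72 per arm. That stands too, but it is a different target from the one in section 2.3. If one point is a within-group change, d = 0.32 would fit only an extreme SD of the change score.

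A reader might also infer that the dropout allowance is wrong, since 120/0.8 = 150. The text states a 20% increase and not a 20% loss rate, so 144 is correct as written. Likewise, the lack of an effect size for attitude is a detail that an article may leave to the full protocol, because no power is claimed for it.

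The test, sidedness and correlation may also be given in a document not shown. That explains their absence, but the printed power figure remains one that cannot be read as the trial's between-group power. Finally, nothing in the article plans to treat a null result as evidence of no effect, so that risk lies in how others use the 80%.

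**Conclusion.** The concern holds in a limited form. The statement that 60 children give 80% power at d = 0.32 fits a one-group, one-sided pre-post test, or an interaction larger than 0.32 SD. It does not hold for a between-group d of 0.32, which needs about 155 per arm unadjusted. At the planned size the power for that difference is 41% (120 analysed) to 48% (144), or 52% to 68% with 120 after baseline adjustment, all before clustering.

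This rests on two-sided 5% testing, equal arms and an assumed baseline correlation of 0.5 to 0.7. A correlation near 0.8 would bring 120 to 80% power before clustering, but section 2.3 states none. The Discussion is inconsistent with section 2.3 both in the outcome that 144 serves and in the size of effect. The document does not show that the trial is too small for the difference its authors care about, because it does not settle what that difference is.

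**What to change.** Keep enrolment at 144 and correct the text.

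1. In section 2.3, state which effect d = 0.32 describes (within-group change, group-by-time interaction, or difference between arms), the test, its sidedness, the assumed correlation, and whether 60 is a total or per arm.
2. Withdraw the 80% power claim for a between-group d of 0.32.
3. Report the between-group effect detectable with 80% power: d about 0.52 with 120 analysed and 0.47 with 144, or about 0.45 with 120 and baseline adjustment at an assumed r of 0.5. Say that all of these grow once a design effect for clustering is applied, and give the intraclass correlation and class size used.
4. In the Discussion, align the outcome, number and effect size with section 2.3, and give the SD that links one point to the standardised effect.
5. Optionally, note that 144 retains 120 children for losses up to 16.7%.

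The cost is a rewritten paragraph, one changed Discussion sentence and a less favourable detectable effect. No extra children are needed. The Discussion says implementation is still to come, so the correction can be made before results are known.

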### 2.4. Allocation to Groups

The distribution of the groups will be based on convenience as judged by experts (see the study flow in Figure 1). The intervention group will be made up of children whose teachers have communicated their wish to actively participate in the program. Teachers need to be involved in the intervention as they are aware of the situation in each classroom and it is necessary to carry out the activities correctly inside and outside the classroom.

As stated, the participants in the study will be students in the last cycle of primary education (10–12 years). The intervention will be carried out with pupils in the first year of this cycle (10–11 years) as, at this point, they acquire knowledge about nutrition and begin to develop scientific competence. All pupils in the same school, academic year and group should be part of the intervention group, since, from an ethical point of view, all groups should acquire the same knowledge during the school year. The control group will be formed by the students in the second year of the last cycle of the same primary school (11–12 years). 

### 2.5. Intervention

#### 2.5.1. Intervention Design

This nutrition education program is adapted to the curriculum of the Spanish schools. The intervention will consist of 8 sessions and the main goals will be (1) to understand the balanced diet and to apply it to one’s own diet, (2) to learn what CD and gluten are, and (3) to promote social inclusion of people with CD.

As aforementioned, it is an intervention based on competencies and respective learning outcomes. Therefore, to design the program, the first step was to define the competencies that children will develop during the intervention (Table 1). These competencies were then organised into learning outcomes, according to Bloom’s degree of cognitive abstraction [38,39] from level 1 to 6, and some activities were designed in order to develop these learning outcomes [40]. 

As mentioned, the teaching methodology chosen to develop learning outcomes is inquiry-based learning (IBL), which has proven to be very effective in science teaching–learning processes [41]. As a result, an inquiry-oriented teaching-learning process was developed, focused on facilitating children’s understanding of the research process. The teaching–learning process will be developed through games and experiments related to the topic of each session, described in Table 1. It must be noted that some topics will be transversally learnt along the intervention. In other words, content from some sessions will influence the achievement of various learning outcomes.

The whole intervention will last 4 weeks; 8 face-to-face sessions (one topic each) will be held during school hours, with 2 sessions per week (Table 2). Each session will last one hour. In addition to the session, each student will have to carry out several tasks at home together with their families, in relation to what they have learnt in class, to reinforce it through family involvement.

The intervention includes activities aimed at encouraging attitudinal and behavioural change related to healthy diet beyond the classroom. Among them, the most important is the “healthy snacks challenge”. This challenge aims to promote healthy mid-morning snacking among pupils. To this end, in the second session of the intervention, students will be divided into groups. Every day (during the month of the intervention), the children will write down their mid-morning snack in a specific section of a workbook. On the last day of each week, the people who are part of the research team will be in charge of giving the corresponding scores for the snacks. Healthy snack, 1 point (fruit, natural dairy products, dried fruit, vegetables, etc.); medium-healthy lunch, 0.5 points (in addition to the aforementioned foods, it includes some unhealthy food); and unhealthy lunch, 0 points (industrial pastries, biscuits, milkshakes or industrial juices, etc.). 

As mentioned above, the children will compete in groups. In this way, collaborative work will be encouraged, where everyone must strive to achieve a common goal. Likewise, every day, they will address the concept of a healthy diet. 

The necessary material for the Zeliakide program has been already designed. A teaching unit has been produced that includes the following material: a notebook containing the contents of the intervention, a virtual classroom where participants can view the contents of each day and interact with the researchers, and the material to carry out the proposed experiments and games (worksheets, power points, laboratory equipment, online games). In order to provide innovative digital material to the classrooms, an augmented reality application that contains all the information in the notebook has also been designed. Through this application, students will be guided by an avatar, a virtual researcher, who will help them carry out the experiments.

